### **6.5.2.3 Second Stage Data Collection**

#### *6.5.2.3.1 Nested Cohort Procedures Overview*

Randomly selected nested cohort MIPs will undergo written informed consent, complete a structured questionnaire about their experiences with CFL models and other health services, and undergo one-time HIV testing (i.e. by collecting a dried blood sample [DBS] from the mother for viral load testing and either performing rapid HIV-1/2 antibody testing or collecting a DBS sample on the HEI for HIV infection ascertainment, as indicated based on HEI age per national testing guidelines).

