#### 6.5.2.3.5 *Nested Cohort Maternal and Infant Viral Load Ascertainment*

Study staff will support routine HIV laboratory monitoring at MOH ART clinics in selected districts for maternal nested cohort participants. Consenting nested cohort participants on ART, including HIV-infected mothers and infants/ young children on treatment, will undergo blood sample collection for quantitative HIV-1 viral load (RNA PCR) testing according to national guidelines. Depending on the standard practice already in place at the facility, blood sampling may proceed by venipuncture (i.e. 10 ml of whole blood) or by finger prick for DBS collection (i.e. 1 DBS card containing 5 wells of approximately 50 µL each, or 250 µL total) for mothers and by DBS collection for infants/ young

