children. For participants completing study procedures in the community, blood sampling will proceed by DBS collection. In all cases, we will follow MOH guidelines for the preparation, collection, handling and transport of DBS samples for VL testing. If participants have not undergone MOH-recommended 6-month or 24-month viral load (VL) testing at the time of study consent, samples for “catch up” VL testing will be obtained by study staff for testing at the appropriate MOH-designated laboratory. If these participants have already complied with the recommended MOH VL testing schedule, but do not have a VL test result documented within 3 to 6 months or longer of study consent, study staff will collect a study-specific blood sample for VL testing by venipuncture (i.e. 10 ml of whole blood) or by heel/finger prick for DBS collection (i.e. 1 DBS card containing 5 wells of approximately 50 µL each, or 250 µL total) depending on the age of the participant (e.g. DBS collection for all infants/ young children), sample transportation logistics and participant preference, to be done at the UNC Project Tidziwe Laboratory in Lilongwe. While it is envisioned that most women and infants/ young children will receive VL testing at approximately 6 and 24 month post-ART initiation per national guidelines, VL testing may occur outside these time points depending on the point at which participants started ART, the timing of study field activities in selected districts, and whether or not the woman or infant/young child accessed routine VL testing through the national program. In cases where the HIV VL returns greater than 1,000 copies/ml, excess blood sample may be sent for HIV genotype/ resistance testing in selected cases to assess for the presence of HIV-1 resistance-conferring mutations, study resources permitting.

All VL test (and any genotype test) results will be returned to the clinic from which the patient was originally identified. We will subsequently inform all patients and mothers of patients that the test results are ready and have been submitted to the clinic. We will recommend they return to discuss these results with the clinic healthcare providers. This will support good clinical care and will also provide additional encouragement to those who have disengaged/ defaulted from care to re-engage.

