Proportion of infants/ young children receiving anti-retroviral therapy (i.e. “Infant ART Initiation”):

Similar to the related maternal indicator, for this infant ART initiation indicator, we will calculate the proportion of HIV-infected infants/ young children initiating ART during the 12 months preceding the evaluation day among all infants with a documented positive HIV test/ evidence of being HIV-positive before the day of evaluation.

Proportion of PMTCT mothers and infants/young children who started ART and have a suppressed HIV

viral load (“Viral suppression”): Using viral load test result data, we will calculate and present separately the proportion of ART-initiated, HIV-infected mothers and ART-initiated HIV-infected infants/ young children who achieved viral suppression. For this final step of the cascade (i.e. the “third 90”), we will use the numerators from the maternal and infant ART initiation indicators for our respective denominators, and will assess the subset of these denominators with documented suppressed viral load test results within 12 months of the evaluation day. We will define viral suppression using a number of established thresholds for HIV-1 viral load, including less than 20 copies/ ml (the lower limit of detection for VL testing performed on plasma collected by venipuncture), less than 550 copies/ml (the lower limit of detection for VL testing performed on DBS) and less than 1,000 copies/ml (the definition of viral suppression used in the recent MOH Malawi Population-Based HIV Impact Assessment).

*7.2.2.3 Maternal IDI Data*

For qualitative data, the same analytical approach will be employed as described for Objective 1 above, except that we will search for patterns in the data that help explain client experiences with CFL model services and navigating the PMTCT care continuum for mothers and their children.

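### Suppression below 20 copies/ml is not limited to plasma, though DBS cannot measure below 550, so model comparisons at that threshold partly reflect specimen type

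*Protocol*

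**What the plan says.** Protocol section 7.2.2.2 calculates the care cascade separately for mothers and for infants/young children, and says at its start that results will be compared across CFL models and SOC. For the third step it states: "We will define viral suppression using a number of established thresholds for HIV-1 viral load". The list is "including less than 20 copies/ ml (the lower limit of detection for VL testing performed on plasma collected by venipuncture", then "less than 550 copies/ml (the lower limit of detection for VL testing performed on DBS", then "less than 1,000 copies/ml (the definition of viral suppression used in the recent MOH Malawi Population-Based HIV Impact Assessment".

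Specimen type is set in section 6.5.2.3.5:
- For mothers, existing facility routine decides: "Depending on the standard practice already in place at the facility, blood sampling may proceed by venipuncture", or by finger prick onto a DBS card.
- Place of sampling overrides this: "For participants completing study procedures in the community, blood sampling will proceed by DBS collection".
- For the study-specific sample, transport logistics and participant preference also play a part.
- Children have no alternative: "DBS collection for all infants/ young children".

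The overview in section 6.5.2.3.1 mentions only one specimen for mothers: "collecting a dried blood sample [DBS] from the mother for viral load testing".

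**The concern.** By the protocol's own detection limits, a DBS card can show that a viral load is under 550 but never that it is under 20. At <20, an undetected DBS result has to be counted as suppressed, counted as not suppressed, or left out. Section 7.2.2.2 neither chooses one of these nor confines <20 to plasma.

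This would only add noise if specimen type were unrelated to the comparison. It is not. Facility practice operates at the level at which CFL model or SOC is assigned. Sampling in the community depends on engagement in care, which the models are meant to change. Two models with identical viral loads could therefore show different proportions under 20 copies/ml.

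**Working it through.** **1. What each specimen can show**, from the limits in 7.2.2.2:

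| True viral load (copies/ml) | Plasma at <20 | DBS at <20 | Either specimen at <550 | Either specimen at <1,000 |
|---|---|---|---|---|
| below 20 | suppressed | undetected, cannot be classified | suppressed | suppressed |
| 20 to 549 | not suppressed | undetected, cannot be classified | suppressed | suppressed |
| 550 to 999 | not suppressed | not suppressed | not suppressed | suppressed |
| 1,000 or more | not suppressed | not suppressed | not suppressed | not suppressed |

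Only the <20 columns depend on the specimen. Every infant study specimen falls in the DBS column, so <20 cannot be assessed there. That needs no assumption.

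**2. The plan's own figures** (section 6.4). SOC suppression is 0.73 × 0.88 + 0.27 × 0.40 = 0.7504, the stated 75%. For 75% against 83% with 298 and 894 mothers and two-sided alpha 0.05:
- pooled proportion 0.25 × 0.75 + 0.75 × 0.83 = 0.81
- null standard error √(0.81 × 0.19 × (1/298 + 1/894)) = 0.0262
- alternative standard error √(0.75 × 0.25/298 + 0.83 × 0.17/894) = 0.0281
- power Φ((0.08 − 1.96 × 0.0262)/0.0281) = 0.846, or 0.826 with continuity correction

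The stated 83% reproduces. The yardstick is an 8-point difference.

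**3. Illustrative size at <20 when the groups truly do not differ.** Let s be the share below 550 copies/ml, m the share at 20 to 549, and d the share of mothers giving DBS.
- Coding A, undetected DBS counted as suppressed: proportion = (s − m) + m·d. The SOC minus CFL gap is m × (d_SOC − d_CFL).
- Coding B, DBS never counted as <20: proportion = (s − m)(1 − d). The gap is −(s − m) × (d_SOC − d_CFL).

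Assumptions not in the documents: s = 0.75 in both groups; m between 0.03 and 0.15; specimen type unrelated to viral load.

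*DBS from tracing only.* Table 3 expects tracing for 0.27 of SOC and 0.20 of CFL mothers. Suppose all traced mothers give DBS and all others plasma, so the difference in d is 0.07.
- A: 0.03 × 0.07 = 0.2 points to 0.15 × 0.07 = 1.1 points, SOC appearing higher.
- B: 0.72 × 0.07 = 5.0 points to 0.60 × 0.07 = 4.2 points, SOC appearing lower.
- B with the 40% out-of-care suppression of section 6.4 applied to traced women: SOC loses 0.27 × 0.40 = 10.8 points and CFL 0.20 × 0.40 = 8.0, a gap of at most 2.8 points.

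*DBS from facility practice.* A purely hypothetical split of all-DBS in SOC and half-DBS in CFL gives a difference in d of 0.5.
- A: 0.03 × 0.5 = 1.5 points to 0.15 × 0.5 = 7.5 points, SOC appearing higher.
- B: 0.72 × 0.5 = 36 points to 0.60 × 0.5 = 30 points, SOC appearing lower.

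Table 1 expects only six SOC sites (two each in Lilongwe, Mzimba and Zomba), so an even balance of facility practice cannot be taken for granted. The direction of the artefact changes with the coding rule. Leaving DBS out altogether would remove everyone sampled in the community from the <20 result, which would then describe a different population.

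**The case against.** The best defence is that the parentheses in 7.2.2.2 are specimen-specific: 20 is meant for plasma, 550 for DBS, and <1,000 is the common cut-off. That is a natural reading, and the text does not say outright that all results are pooled at <20. But it does not state the specimen-specific rule either, and the rule would not help. A mother at 20 to 549 would be unsuppressed on plasma and suppressed on DBS, which is exactly coding A.

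Other points stand in the plan's favour:
- Suppression is a secondary outcome in 7.1, although the title of Table 2 calls its outcomes primary. Sample size was set on retention.
- A threshold that both specimens can classify is already listed. It also matches the level used for genotyping (6.5.2.3.5) and referral (9.6).
- Tracing only stands in for place of sampling. Traced women may come to the clinic, and women in care may be seen in the community (6.5.2.3.3, 6.5.2.3.8).
- Section 6.5.2.3.1 is an overview, so its difference from 6.5.2.3.5 may be loose wording.

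A reader might infer that the suppression threshold will be picked after the data are seen. The protocol does not show this, because ranking thresholds and coding undetected results are commonly left to the statistical analysis plan, which is not available. A reader might also infer a bias of 5 to 15 points. That would compare an all-DBS facility with an all-plasma one under an assumed 20 to 549 share. It is not an effect on the model comparison, and the documents do not give that share.

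**Conclusion.** The point holds for one of the three thresholds. As written, <20 is a definition of suppression for mothers and infants that is not limited to the specimen able to measure it. Comparisons across models and SOC at <20 therefore partly reflect specimen type wherever the mix differs, and nothing in the design equalises the mix. For infants' study specimens <20 is not measurable.

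The size cannot be determined from the documents. It depends on the share of mothers at 20 to 549 copies/ml, on how undetected DBS is coded, and on how specimen type differs between models. The tracing-only range of about 0.2 to 5 points in absolute size is an illustration under the assumptions above; facility practice that differed by model would add to it. Neither the primary retention outcome nor suppression at <550 or <1,000 is affected, so this does not undermine the suppression comparison as a whole.

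**What to change.** In section 7.2.2.2:
- Name <1,000 copies/ml as the definition for comparing suppression across CFL models and SOC. It is already listed, and both specimens can classify it.
- Keep <550 as a sensitivity threshold.
- Report <20 only descriptively and only for plasma specimens: not for infants' DBS, and not as a between-model comparison.

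Record specimen type with each viral load result. Reconcile 6.5.2.3.1, which mentions only DBS for mothers, with 6.5.2.3.5, which allows venipuncture or DBS.

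The cost is protocol wording and one recorded data item. The downside is that the <20 result becomes a description of women who gave plasma, and no longer speaks for those sampled in the community.

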## 8.0 Results Dissemination & Expected Results

### 8.1 Results Dissemination Strategy

Dissemination of results will occur through three mechanisms: 1) a report to the NHSRC and HIV Unit of the Ministry of Health; 2) a presentation at the annual National AIDS Commission research dissemination meeting; and 3) a manuscript published in an international, peer-reviewed journal. All presentations, abstracts, and manuscripts derived from this impact evaluation will be made available for review by our partners, including NHSRC and the HIV Unit of the Malawi Ministry of Health.

The primary audience for results dissemination and utilization will be policy makers and program managers working on PMTCT programs in Malawi and elsewhere in sub-Saharan Africa. To ensure that we reach our target audience, stakeholder engagement will be a major, continuous focus of the project from the time of protocol development through study conclusion. In addition, to ensure that our study is conducted to the highest ethical and methodological standards, and that it addresses relevant evidence gaps, we will convene a Study Advisory Committee (SAC). The SAC's role during the study will be to provide guidance and strategic recommendations on stakeholder engagement and the direction, performance, and results of the study to ensure the best achievable outcome within the time frame and financial resources available. During study implementation, the SAC will meet periodically by teleconference or in-person, realistically no more than twice annually, and will be asked to provide input and suggestions on: the study protocol; study operations to meet the study objectives; dissemination and stakeholder/ community engagement; data analyses and possible sub-studies; and strategies to support inclusion of relevant lessons learned into district, national, and regional policy. We will appoint at least 3 experts to the SAC with knowledge of the subject matter and context, each of whom will provide guidance to the study team. Among these experts, we will include at least one UNC faculty expert, one high-level government official from the Malawi Ministry of Health, one member of the USAID/Malawi health team, one member of the district health management team from a selected district with experience in community-based service delivery (e.g. the District Health or Nursing Officer), representatives from NGO focused on providing CFL services (e.g. mothers2mothers, Tingathe, and Dignitas), as well as one or more other prominent local experts who have extensive prior research experience. SAC members will be invited to comment on circulated first drafts of the study protocol and survey, interview guides, and other study tools either virtually, or preferably, during a pre-launch SAC meeting or teleconference.

Interim and final study results will be shared with the HIV Unit/ MOH, USAID, and other stakeholders. We will report all interim results available through the end of calendar year 2017 and early 2018 to HIV Unit/ MOH, USAID/Washington and USAID/Malawi at that time. Interim results will also be presented via a study brief and PowerPoint in mid-2018 at a local dissemination meeting held at UNC Project headquarters. Final study results will be presented at a national-level dissemination meeting in mid-to-late 2019 that will include a PowerPoint presentation, information about data sharing and a discussion with stakeholders about the interpretation of results and action plans for their use. A full report or a summary document will also be distributed at the meeting.

## 8.2 Community Engagement

We will engage the community in catchment areas where we plan to conduct study activities through a variety of mechanisms, including through our CFL program partners who maintain strong ties to the community, as well as via pre-launch community sensitization activities. We will work with the UNC Project—Malawi Community Advisory Board to proactively address any concerns presented by the community throughout the life of the study, and to develop appropriate community messaging about study activities and findings. Finally, we will hold district-level dissemination meetings following national-level dissemination to ensure that important study findings are shared with the community participants and health workers who made the study possible.

## 8.3 Expected Results

We expect this study will provide evidence about the role of CFLs in improving MIP health outcomes and supporting HIV-positive mothers to navigate the PMTCT continuum of care. We expect this research to generate a clear typology of CFL models that will enable common terminology, and a shared focus on the most essential elements of CFL models, to be used among stakeholders when discussing strategies for retaining MIPs in PMTCT programs in the region. Lastly, we envision that our study will identify those components of community-based client support that are associated with maternal retention in care and infant HIV-free survival, helping to refine and accelerate scale up of promising CFL models in Malawi and elsewhere in sub-Saharan Africa.

## 9.0 Ethical considerations

### 9.1 Overview

As we propose to use largely existing routine care data, the risks incurred with the study activities described herein are minimal. The principal risk involved is the possibility of an inadvertent disclosure of confidential patient health information, which could include HIV status. At all steps of the study, we will protect participant privacy and confidentiality to reduce this risk.

### 9.2 Physical Risks

Blood sample collection carries a small risk of pain, bleeding, bruising, and (in rare cases) infection. To minimize these risks, the following measures will be taken: 1) only properly trained study staff will perform or support MOH-led blood sample collection activities; 2) the PI will review with study staff how to properly carry out phlebotomy procedures; 3) sterile technique will be used for all blood draws; and 4) we will seek to obtain specimens at only one time point. Based on these measures, the magnitude and likelihood of phlebotomy risk is expected to be consistent with those normally encountered during the course of routine medical care for healthy persons.

### 9.3 Psychosocial Risks

Study participants may become embarrassed, worried, anxious, or uncomfortable when discussing sensitive topics during FGDs or IDIs, when answering questions from the nested cohort questionnaire, or when approached during tracing activities in the community. Study staff will be trained how to identify and mitigate issues that may cause psychosocial distress, and will use established counselling techniques when discussing participant challenges with HIV care. There is also a risk of inadvertent disclosure of HIV status or other personal health information.

### 9.4 Methods to Minimise Risk

All participants will be instructed during the informed consent process that they may discontinue any study procedure, including questionnaires and IDIs at any time for any reason, such as experiencing psychosocial stress related to any question(s). Risks relating to psychological discomfort will be further minimized by: 1) reducing respondent burden through streamlining of questionnaires and IDI guides; and 2) referring participants to appropriate counselling, as necessary. We do not anticipate that focus group discussions will pose any risk of psychological discomfort to stakeholders beyond that encountered in the course of everyday professional conversations. However, due to the potentially

sensitive nature of questions surrounding perceptions of the functionality of the health system or CFL models, we will ensure through a comprehensive verbal informed consent process that participants are aware of: 1) their right to withdraw; 2) their right to not respond to any question(s) they do not wish to answer; and 3) that their responses will not be linked back to them in any way or shared with their employers or supervisors.

We will strive to minimize the risk of unintended confidentiality breaches involving study-related information by: 1) integrating our study procedures within routine health-related operations whenever possible so as not to draw attention to study participants; 2) conducting nested cohort enrolment procedures, IDIs, and FGDs in private settings that are conveniently located for participants such that all information is kept strictly confidential and not inadvertently disclosed to anyone not involved in the study activity; and 3) engaging trained CFL providers to continue providing routine stigma mitigation messaging and report any instances of harassment to the study team.

We will use our team's previous experience with patient tracing under the OHTA project to ensure patient confidentiality is maintained at all times. Tracers will be well-trained and will only state generic health-related purposes or other socially acceptable, non-identifiable reasons for any home visits. We will also work closely with HSAs and CFL providers whenever possible, and will ensure that there is a female research assistant or other female colleague present for all tracing activities to ensure maximal gender sensitivity during study activities. Study staff involved in tracing will not wear any identifiable clothing or badge when making home visits. All study staff members will be trained in appropriate implementation methods.

All information collected on paper during the course of this study will be kept securely and confidentially in a locked cabinet. Case report forms will be identified using the participant's study number only. All identifying study information, including participant locator information used for tracing activities, will only be available to study staff and will be stored securely, separately from the other information we collect from participants. Any other information we collect will be identified on forms and computer or tablet files by a study number only, not the participant's name or other identifying information. Information entered into the study database will be kept separately from participant identifying details and protected by a password. Only restricted study staff will have access to and be able to link identifying details with study data, ensuring that the participants' information

remains confidential. Indeed, data security measures will be strictly adhered to, including the immediate de-identification of data for analysis and the storage of data on secure, password-protected servers and encrypted computers and tablets.

Participant information will remain confidential at all times, unless we are required by law to release information. Reports about the study and results that may be published in scientific journals will not include any identifying information that would allow participants identities to be revealed or deduced.

